***Sample size***

For populations with case-level depression, a successful treatment outcome has been defined as 5 points on the PHQ9 [41]; however, this was calculated using distribution methods, which are not currently advocated [42], and does not incorporate our wider population of interest. In an older population with subthreshold depression a difference of 1.3 has been found to be clinically and cost-effective [43] with a standard deviation of 4, equating to a standardised effect size of 0.325. An effect size of 0.3 is assumed for this calculation, which is also in line with pooled standardised mean differences found in a meta-analysis of previous trials of collaborative care [44]. Assuming 90% power, 5% alpha, 0.3 effect size and 20% attrition (from mortality and loss to follow-up) the trial would need to randomise 590 participants. However, this calculation is very conservative. In the primary analysis, baseline PHQ9 score shall be included as a covariate, which will result in gains in power. Therefore, accounting for the correlation between baseline and outcome PHQ9 score can reduce the required sample size. In the external pilot trial, a correlation of 0.58 was observed between the PHQ9 score at baseline and three months amongst participants who scored ≥5 at baseline, and follow-up at three months was 90% [23]. Assuming a correlation of at least 0.5, 90% power, 5% alpha, 0.3 effect size and 10% attrition, 392 participants would need to be recruited and randomised into the trial. Calculations conducted using Stata v15.

***Statistical analyses***

A detailed statistical analysis plan will be produced prior to data analysis and approved by the joint Programme Steering and Data Monitoring and Ethics Committee. Analysis will be conducted on an intention to treat basis, using two-sided statistical tests at the 5% significance level, using Stata v17 or later. The statistician will not be blinded to treatment allocation.

The flow of participants through the trial will be detailed in a CONSORT diagram [Figure 2]. The number of individuals screened, eligible and randomised will be presented, with reasons for non-participation provided where available. Intervention adherence will be recorded and reported, including the number of sessions completed. The number of participants withdrawing from the intervention and/or the trial and any reasons for withdrawal will be summarised by trial arm.

Participant baseline data will be summarised descriptively by trial arm, for all randomised participants and for all who are included in the primary outcome analysis. No formal statistical comparisons will be undertaken on baseline data. Continuous measures will be reported as means and SD, while the categorical data will be reported as counts and percentages.

The primary outcome (PHQ9) will be analysed using a linear mixed model, incorporating data from all post-randomisation follow-up time points (one, three and 12 months). The model will include time, trial arm, an arm-by-time interaction, and baseline PHQ-9 score as fixed effects, with participant nested within site as random effects. The model will provide an overall treatment effect over time as well as estimates at individual time points, which will be reported as mean differences, 95% confidence intervals and p-values. The primary time-point of interest is pre-specified at three months.

The secondary outcomes of GAD7, De Jong Gierveld Scale, Lubben Social Network Scale, and SF-12v2 (mental and physical health component scores separately) will be similarly analysed.

A complier average causal effect (CACE) analysis will be conducted for the primary outcome to account for non-compliance with the intervention.

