Participants will be offered up to eight intervention sessions, delivered by a trained BSW and supported by the self-help booklet. The self-help booklet has been developed over a number of similar studies; most recently during the BASIL-C19 pilot study [23], where it was adapted for use during the COVID-19 pandemic with help and feedback from older adults, BSWs and a range of stakeholders, including members of the existing MODS/BASIL Patient and Public Involvement (PPI) group. Further minor adaptations were made for BASIL^+^ following the BASIL-C19 pilot (including minor design and wording changes to the self-help booklet). All sessions will be delivered remotely, either over the telephone or by video call (where this is available and preferred) and according to participant preference. The first session will last approximately one hour with subsequent sessions lasting approximately 30 minutes.

The depression scale of the Depression Anxiety Stress Scale (DASS) [30] will be used as a within session depression symptom monitoring tool. The DASS is a widely used and simple to score monitoring tool with clear clinical cut off scores (non/mild/moderate/severe). DASS scores will be used to aid decision making by BSWs in conjunction with their BASIL^+^ clinical supervisor. Where risk or significant clinical deterioration is indicated the participant will be supported to access more formal healthcare interventions.

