***BASIL^+^ Support Workers (BSWs)***

BSWs will have a range of backgrounds (clinical and non-clinical). They will be required to complete bespoke intervention training (approximately 22 hours) facilitated by clinical members of the study team. Materials, including recorded presentations, role-play demonstration of sessions and a support worker treatment manual will be provided to the BSWs prior to three, two-hour online/video group training sessions. The training will cover the components of the BA intervention within the Collaborative Care framework, intervention delivery, and study procedures. BSWs will be required to pass a telephone-based bespoke competency assessment with a training facilitator before commencing delivery of the intervention. BSWs will receive regular supervision/support from a clinical member of the BASIL^+^ study team.

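### The primary model and the 392-participant calculation make no allowance for clustering by support worker, which arises in the intervention arm only

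*Protocol*

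**What the plan says.** **Delivery.** The BASIL+ intervention section says: "Participants will be offered up to eight intervention sessions, delivered by a trained BSW and supported by the self-help booklet". The worker and participant build an individual plan together. The section on support workers adds that "BSWs will have a range of backgrounds (clinical and non-clinical"), and describes common training, a manual, a competency assessment and continuing supervision. Under Comparator, controls get usual care and signposting, with no support worker.

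**Model.** Statistical analyses specifies a linear mixed model for PHQ-9 at one, three and 12 months. Its fixed effects are time, arm, their interaction and baseline score, "with participant nested within site as random effects". Tests are made "using two-sided statistical tests at the 5% significance level". The main secondary scales (GAD7, De Jong Gierveld, Lubben, SF-12v2) are to be analysed in the same way. A detailed SAP is promised but is not at hand.

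**Sample size.** The operative calculation reads: "Assuming a correlation of at least 0.5, 90% power, 5% alpha, 0.3 effect size and 10% attrition, 392 participants would need" to be randomised. The support for the correlation is that in the pilot "a correlation of 0.58 was observed between the PHQ9 score at baseline and three months". No ICC, caseload or design effect appears.

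**The concern.** Participants are randomised individually, but those in one arm are then grouped by the person who treats them. This is a partially nested design. If BSWs differ in how much good they do, outcomes within one BSW's caseload are correlated, while control outcomes are not correlated in this way.

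The listed random effects do not represent this. The site intercept is shared by both arms, so it largely cancels from the treatment contrast and cannot carry variance found in one arm only. The participant intercept absorbs BSW variance, but treats it as independent from one participant to the next. The estimated standard error of the three-month difference would then be too small, the interval too narrow and the p-value too low. The secondary scales inherit the same structure. The power statement has the same gap, because it counts intervention participants as fully independent.

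**Working it through.** **Inputs from the protocol:** standardised difference 0.3; two-sided 5% alpha; 90% power; baseline-to-outcome correlation r = 0.5 (0.58 in the pilot); 10% attrition; 1:1 allocation; N = 392.

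**Assumptions, not in the protocol:** number of BSWs K and ICC. The nearest figures are up to 20 BSWs to be interviewed (Qualitative process evaluation) and about 12 study sites (SWAT section). I take K = 20 to 40 as the main range, K = 12 as an extreme, and ICC = 0.01 to 0.05 on the baseline-adjusted variance. I also assume equal caseloads and one BSW per participant.

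**Step 1: reproduce 392.**
- Per arm, unadjusted: 2 × (1.96 + 1.2816)² / 0.3² = 233.5.
- Times (1 − 0.5²) = 0.75: 175.1, rounded up to 176.
- 2 × 176 / 0.9 = 391.1, rounded up to 392. This is an exact match with no clustering term.
- Check on the unadjusted figure of 590: 2 × 234 / 0.8 = 585, or 2 × 235 / 0.8 = 587.5 with a t-based calculation. Both are close to 590, again with no design effect.

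**Step 2: unclustered power with 176 analysed per arm.**
- r = 0.5: SE = √(0.75 × 2/176) = 0.0923; power = Φ(0.3/0.0923 − 1.96) = 90.1%.
- r = 0.58: SE = √(0.6636 × 2/176) = 0.0868; power = 93.3%.

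**Step 3: add clustering in one arm.**
- Mean caseload m = 176/K.
- Intervention-arm design effect DE = 1 + (m − 1) × ICC.
- Variance factor for the difference F = (1 + DE)/2.
- True SE = unclustered SE × √F.
- Power with the correct SE = Φ(0.3/true SE − 1.96).
- Type I error if clustering is ignored = 2 × [1 − Φ(1.96/√F)].

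Example, K = 20 and ICC = 0.05: m = 8.8; DE = 1 + 7.8 × 0.05 = 1.39; F = 1.195; √F = 1.093. True SE at r = 0.5 is 0.1009. Power = Φ(2.97 − 1.96) = 84.4%. Type I error = 2 × [1 − Φ(1.793)] = 7.3%.

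| K | ICC | True SE larger by | Type I error | Power, r = 0.5 | Power, r = 0.58 |
|---|---|---|---|---|---|
| 40 | 0.01 | 0.8% | 5.2% | 89.7% | 92.9% |
| 40 | 0.02 | 1.7% | 5.4% | 89.2% | 92.5% |
| 40 | 0.05 | 4.2% | 6.0% | 87.7% | 91.3% |
| 20 | 0.01 | 1.9% | 5.5% | 89.0% | 92.4% |
| 20 | 0.02 | 3.8% | 5.9% | 87.9% | 91.4% |
| 20 | 0.05 | 9.3% | 7.3% | 84.4% | 88.5% |
| 12 | 0.01 | 3.4% | 5.8% | 88.2% | 91.7% |
| 12 | 0.02 | 6.6% | 6.6% | 86.2% | 90.0% |
| 12 | 0.05 | 15.8% | 9.1% | 80.1% | 84.7% |

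**Step 4: how much ICC the pilot correlation can absorb.** At r = 0.58, 90% power allows F up to (0.3/3.2415)² / (0.6636 × 2/176) = 1.136, so ICC ≤ 2 × 0.136/(m − 1). That is about 0.035 for K = 20, 0.08 for K = 40 and 0.02 for K = 12.

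The type I error column does not depend on r. Unequal caseloads would make the figures somewhat worse.

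**The case against.** A reader might infer that the standard errors are definitely too small and that 90% power is not delivered, or that it survives only if BSWs have no effect at all. The protocol does not support that. Both statements turn on an ICC and a number of BSWs that it does not give. At the pilot correlation, power stays at 90% or more for ICCs up to the limits in Step 4, and assuming a correlation of at least 0.5 left a deliberate margin.

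Other points also stand:
- Common training, the manual, the booklet, the competency assessment and supervision may keep the ICC small.
- Intervention participants who never engage dilute the clustering in an intention-to-treat analysis.
- One BSW per site has no textual support. Planned selection among BSWs for up to 20 interviews points to a larger pool than 12.
- The type I error figures apply when BSW effects vary around a zero mean and inference is to BSWs more widely. If the intervention changed nothing for anyone, this inflation would vanish.

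Two replies do not succeed. A higher baseline correlation recovers power but leaves the proportional understatement of the standard error unchanged. Deferral to the SAP does not settle the matter either, because the protocol already states the random effects and the power. An SAP that follows it repeats the omission, and one that adds a BSW term departs from it.

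**Conclusion.** The concern holds in conditional form. The model and the 392 calculation contain no allowance for one-arm clustering by BSW. This follows from the protocol's own text and from the exact reproduction of 392.

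The consequence is modest over the main range of K = 20 to 40 and ICC 0.01 to 0.05: type I error of about 5.2% to 7.3%, with power of about 90% to 84% at r = 0.5 and about 93% to 88% at r = 0.58. With as few as 12 BSWs it would be worse. These sizes rest on assumed values and on the equal-caseload approximation, for the three-month contrast only.

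It deserves correction before analysis, but it does not call the design or the recruitment target into question.

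**What to change.** 1. In Statistical analyses, add to the primary and secondary models a BSW random effect acting in the intervention arm only, with controls as singletons, and use a small-sample degrees-of-freedom correction. At minimum, pre-specify this model as a sensitivity analysis. Align protocol and SAP on whichever is chosen.
2. Report the number of BSWs, their caseloads and the estimated BSW ICC.
3. In Sample size, state that the 90% power is conditional on no BSW clustering, and give a range over plausible ICCs and numbers of BSWs.

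The change should be fixed before analysis, because the statistician is not blinded and a later addition could look driven by the data.

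The cost is a BSW identifier in the analysis file, one model term, slightly wider intervals and a slightly less favourable power statement. No extra participants are needed.

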***Economic Evaluation***

A trial-based economic evaluation from UK NHS and personal and social services (PSS) perspective will be conducted in order to evaluate the cost-effectiveness of the BA intervention compared to usual care for the target population. Health outcomes will be measured in terms of quality-adjusted life years (QALYs) using the EQ-5D-3L [37] questionnaire and calculated using standard area-under-the-curve method based on individual responses over the study period (45, 46). Costs of intervention and health service use will be calculated using a bottom-up costing approach. Resources used to deliver the intervention will be obtained from the study team, whereas health and social service resource use will be measured using a brief, tailored resource-use questionnaire, developed based on the questionnaire used in the BASIL C-19 pilot study [23]. Unit costs of health and social service use will be obtained from the UK national reference costs [47] and the Unit Costs of Health and Social Care report [48]. Cost of other professional support will be estimated from relevant salary scales and published reports/literature. Uncertainty around the incremental cost-effectiveness ratios (ICER) will be captured using non-parametric bootstrapping technique, and the results will be presented in the conventional form of a cost-effectiveness acceptability curve (CEAC). Sensitivity analyses will be conducted to assess the impact of using SF-12v2 to measure QALYs and the impact of including costs of informal care and other additional support.

***Qualitative process evaluation***

The qualitative process evaluation will further explore the acceptability of the intervention, including important elements of the intervention and mode of delivery, barriers and enablers to integrating the intervention into participants’ existing health and care support, and the impact of the intervention on participants’ mood and general wellbeing in the context of the COVID-19 restrictions. Semi-structured interviews will be undertaken with samples of study participants, BSWs and caregivers/supportive others (where they have been involved in the intervention).

Interviews will be conducted with 15-20 participants who complete the intervention (”completers”), and up to 10 participants who were offered the intervention but who did not engage with or who ‘dropped out’ of the intervention. Up to 10 interviews will also be conducted with informal caregivers/supportive others. All participant and caregiver interviews will take place after the primary outcome has been completed.

Interviews will be conducted with up to 20 BSWs and will explore barriers and facilitators to delivery of the intervention and how the intervention might be integrated within health care settings. In order to assist with maximum variation in the experiences of the BSWs interviewed, factors such as intervention site location and demographic factors (such as job role, age and ethnicity) will be used to support selection for interview.

Interview topic guides will vary by participant group and will be modified iteratively as interviews and analyses progress. All interviews will last up to approximately 30-45 minutes and will be conducted over the telephone or a virtual platform.

Study participants provide consent to taking part in a qualitative interview as part of a set of optional consent statements (with form part of the trial consent form) upon entry to BASIL+.

BSWs will obtain verbal permission from interested caregivers/supportive others for the BASIL^+^ study team to send them (post/email) a study information pack (containing an invitation letter, participant information sheet and example consent form) followed by telephone contact from the study team to discuss the study. For caregivers/supportive others who agree to take part in an interview, verbal consent will be taken (and audio recorded) prior to the interview.

BSWs will receive a study information pack (containing an invitation letter, information sheet and example consent form) following BSW training. They will be invited to complete an online consent form or to contact the qualitative study team directly to indicate their interest in taking part in an interview.

All interviews will be digitally-recorded (with participant consent), anonymised and transcribed, the transcripts forming the data for analysis. Verbal consent for interview participation will be taken (and recorded) before the interview commences. An initial thematic analysis will be conducted. Coding will be undertaken independently by members of the qualitative research team with meetings to ensure emerging codes remain grounded in the original data. A framework approach [49, 50] will be used to analyse the data, sensitised by the Normalisation Process Theory (NPT) [51] to explore barriers and facilitators to rapid implementation of the BASIL^+^ intervention into routine practice.

***Patient and Public Involvement***

Our Patient and Public Involvement (PPI) Advisory Group (AG) was originally convened for the MODS programme of research and currently consists of a group (N=8) of individuals with a range of lived experience of physical and/or mental comorbidities and caregivers.

The PPI AG have extended their support to the BASIL research programme. Members of the research team have met virtually with the PPI AG on several occasions since the start of the COVID-19 pandemic. The PPI AG members provided feedback on the design and implementation of the BASIL+ trial, including the development of remote recruitment methods and materials (including the Participant Information Sheet) and plans for the remote delivery of the BASIL+ intervention and trial to include adherence to COVID-19 restrictions.

In addition to the work with the advisory group, the MODS/BASIL research programmes have PPI representation at Programme Management Group (PMG) meetings and on the independent Programme Steering and Data Monitoring and Ethics Committee (PSC).

***Status and timeline of the study***

Recruitment of participants began in February 2021 and is expected to be completed by the end of February 2022. Intervention delivery is expected to be completed by March/April 2022 depending on participant availability. The current protocol is version 4.0 dated 13/12/2021.

**Discussion**

To the best of our knowledge, BASIL^+^ represents the first large-scale mental health randomised controlled trial conducted in response to the COVID-19 pandemic with the aim of mitigating the psychological impacts of the pandemic and associated social restrictions on potentially vulnerable older adults. The prevalence of depression and loneliness is expected to have increased in the general population due to COVID-19; this increase may have a disproportionate negative impact on older adults with existing long-term health conditions.

We adapted an evidence-based low intensity BA intervention, previously found to be effective at reducing depressive symptoms in older adults [52], for use during the pandemic. The brief nature of the intervention lends itself to remote delivery and could represent an efficient and effective way to support vulnerable populations by reducing depression and loneliness, particularly during periods of social isolation, such as the COVID-19 pandemic. The study has the potential to lead to significant benefits to the NHS, health and social care settings, and society.

BASIL^+^ will also add to existing trial based evidence in this area. There are few trials of cognitive or behavioural interventions [53], and we anticipate this will be the largest such trial. In time we anticipate that the results of BASIL^+^ will contribute to Cochrane reviews in this topic [54].

BASIL^+^ builds on the work conducted in the BASIL-C19 external pilot RCT [23] and will provide further lessons for the efficient delivery of mental health trials beyond the pandemic. The current work will be important in contributing to the emerging knowledge that trials can be conducted more efficiently and resourcefully when networks and research communities come together to work collaboratively with a united goal.

**Ethical considerations and declarations**

The trial received ethical approval from Yorkshire and The Humber – Leeds West Research Ethics Committee on 11 December 2021 (REC Ref: 20/YH/0347). The sponsor for BASIL^+^ is Tees, Esk and Wear Valleys NHS Foundation Trust.

Although we are aware that the study population could be considered a vulnerable group, we do not anticipate any major ethical issues. The study will be conducted to protect the human rights and dignity of the participant as reflected in the 1996 version of the Helsinki Declaration. In order to protect the study participants, the following provisions will be made/upheld; the study has been designed to minimise pain, discomfort and fear and any foreseeable risk in relation to the experiences/treatments involved, the explicit wishes of the participant will be respected including the right to withdraw from the study at any time, the interest of the patient will prevail over those of science and society, provision will be made for indemnity by the investigator and sponsor. Patients will not be denied any form of care that is currently available in the NHS by participating in the study.

Protocol amendments will be managed via the Health Research Authority, Research Ethics Committee and sponsor approvals process during the study.

***Acknowledgements***

We would like to thank: the participants for taking part in the trial, general practice and North East and North Cumbria Local Clinical Research Network staff for identifying and facilitating recruitment of participants, the independent Programme Steering Committee members for overseeing the study, and our PPI AG members for their insightful contributions and collaboration.

